### Study Sites

All 15 PCPs in the urban Hawkes Bay region of Aotearoa New Zealand were approached; 8 provided informed written consent to participate in the cluster randomized clinical trial and were randomized: 4 to intervention and 4 to control. All pregnant women enrolled as a patient of an intervention PCP are eligible for the intervention.

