### Sample Size

A total of 8 practices and 216 Maori participants (4 practices and 108 Maori participants in each group) will provide 80% power at a two-sided α of .05 to detect an 18.5% difference in the proportion of infants who receive all age-appropriate vaccinations by 6 months of age between the groups. For these figures, we have assumed an average cluster size of 27, intracluster correlation coefficient of 0.01, and that 83.5% of the infants will receive all age-appropriate vaccinations by 6 months of age in the intervention group and 65% in the control group. Our total sample size requires 432 pregnancies (216 control, 216 intervention).

Based on the expected recruitment rate and pregnant women meeting the entry criteria for the core intervention (ie, seen in a PCP before 20 weeks of pregnancy), He Korowai Manaaki is offered through intervention practices to all pregnant women for approximately 18 months from the commencement of the study to obtain the required sample size.

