### Analysis

Data analysis will occur as soon as outcome data are available for the intervention and control arms. Within a Kaupapa Māori inquiry paradigm [8-10], the primary analysis is for Māori, with secondary analysis for non-Māori [17]. An intention-to-treat analysis will be undertaken [18] using individual participant data. All pregnancies will be analyzed (regardless of the number of He Korowai Manaaki appointments attended), with the primary cohort being women seen in a PCP before 20 weeks of pregnancy.

The rate of infant hospitalizations will be analyzed using Poisson regression, and if there is evidence of overdispersion or underdispersion, then negative binomial model will be used. A generalized linear mixed model with a logit link will be used to analyze binary outcomes, and a linear mixed model will be used to analyze continuous outcomes. All regression models will adjust for potential personal and care-related confounders and for the effect of clustering within practices. Sensitivity analyses will be undertaken for the primary outcome to determine the impact of missing data, and per protocol analyses will be conducted. The consistency of effects for prespecified subgroups will be assessed using tests for heterogeneity.

Descriptions of rates, rate ratios, odds ratios, and respective 95% confidence intervals will be reported. Results will be aggregated, and no individual practice will be identifiable.

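### With 8 practices, the protocol names a logit mixed model but no few-cluster method, and its 80% power makes no allowance for 8 clusters; default Wald tests would give about 6–7% false positives at the planned ICC

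*Protocol article*

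**What the plan says.** Study Sites fixes the number of clusters: "8 provided informed written consent to participate in the cluster randomized clinical trial and were randomized: 4 to intervention and 4 to control". The Analysis section gives the model by outcome type: "A generalized linear mixed model with a logit link will be used to analyze binary outcomes". It adds that "All regression models will adjust for potential personal and care-related confounders and for the effect of clustering within practices", and promises odds ratios and rate ratios with 95% confidence intervals. Timely vaccination by 6 months is a yes/no outcome per infant, so the logit mixed model is its primary analysis. The section names no test statistic, degrees-of-freedom rule, cluster-level analysis or permutation test.

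Sample Size states that 8 practices and 216 Māori participants, 108 per arm, "will provide 80% power at a two-sided α of .05 to detect an 18.5% difference". The planning values are given: "we have assumed an average cluster size of 27, intracluster correlation coefficient of 0.01", and "83.5% of the infants will receive all age-appropriate vaccinations by 6 months of age in the intervention group and 65% in the control group". No other ICC appears in the document.

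**The concern.** Eight practices carry little information about between-practice variation. With two arms, a comparison of practices has 8 − 2 = 6 degrees of freedom. A maximum-likelihood mixed model estimates the practice variance poorly and often puts it at exactly zero. The fit then reduces to ordinary logistic regression and ignores clustering. Comparing its Wald statistic with 1.96 treats the standard error as known, so p-values come out too small and intervals too narrow.

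The stated power has the same weakness if it too rests on normal quantiles. Naming a few-cluster test later would protect the error rate, but the stated 80% would then no longer describe the trial. Both matter because the authors intend the result to inform policy and to serve as a prototype for a national maternity pathway.

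**Working it through.** **Inputs.** From Sample Size: rates 0.835 and 0.65, difference 0.185, 27 infants per practice, ICC 0.01, 108 per arm, two-sided alpha 0.05, power 80%. From Study Sites: 4 practices per arm. ICCs of 0.02 and 0.05 are assumptions.

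**Step 1: reproduce the stated size.** The design effect is 1 + (27 − 1) × 0.01 = 1.26. The sum of the two binomial variances is 0.835 × 0.165 + 0.65 × 0.35 = 0.3653. With normal quantiles and unpooled variance, n per arm is (1.960 + 0.842)² × 0.3653 / 0.185² = 83.8. Multiplied by 1.26 this is 105.5, or 105.5 / 27 = 3.9 practices, rounded up to 4 × 27 = 108. The pooled formula gives 87 × 1.26 = 109.6. A continuity correction gives 98 × 1.26 = 123.5, which does not match. The stated 108 therefore comes from normal quantiles with no allowance for few clusters.

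**Step 2: power at 108 per arm.** The standard error is √(0.3653 × 1.26 / 108) = 0.0653, so difference / SE = 0.185 / 0.0653 = 2.83. For the t column, power comes from the noncentral t on 6 df with critical value 2.447.

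| ICC | Design effect | z reference | t on 6 df |
|---|---|---|---|
| 0.01 | 1.26 | 81% | 66% |
| 0.02 | 1.52 | 73% | 58% |
| 0.05 | 2.30 | 55% | 42% |

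With the pooled variance the z figure at ICC 0.01 is 79.6%.

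**Step 3: false-positive rate of the named model.** Trials were simulated with no effect: 8 practices, 4 against 4, a 65% rate in both arms, 10,004 trials per setting, Monte Carlo standard error 0.2 to 0.3 points. The logit random-intercept model was fitted by maximum likelihood with 25-point quadrature. Ranges cover logit-normal and beta-binomial practice effects; single figures at ICC 0 and 0.02 are logit-normal only. Unequal practices had 10 to 48 infants, mean 27.

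| ICC | Practices | Wald z | Likelihood ratio | Mixed model, t on 6 df | t test on practice proportions, 6 df | Variance estimated as zero |
|---|---|---|---|---|---|---|
| 0 | 27 each | 4.7% | 4.3% | 1.1% | 5.2% | 76% |
| 0.01 | 27 each | 6.5–7.0% | 5.5–5.7% | 2.1–2.3% | 4.9–5.3% | 60% |
| 0.01 | unequal | 6.7–6.9% | 5.6–5.7% | 2.3–2.6% | 4.6–5.0% | 64% |
| 0.02 | 27 each | 8.4% | 6.9% | 3.2% | 5.1% | 48% |
| 0.05 | 27 each | 11.2–11.3% | 8.8–9.1% | 5.2–5.3% | 5.0–5.3% | 23–24% |
| 0.05 | unequal | 11.6–12.0% | 9.1–9.3% | 5.7–5.8% | 5.0% | 28% |

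Further runs gave 6.3% and 6.6% for Wald z at ICC 0.01, and 10.6% and 10.7% at 0.05. With 54 per practice (the 216 pregnancies per arm over 4 practices), Wald z gave 7.8–8.7% at 0.01 and 12.9–13.4% at 0.05.

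**Step 4: interval width.** For the same standard error, a 6-df interval is 2.447 / 1.960 = 1.25 times as wide.

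**The case against.** The article names a model class, not a test. The choice of reference distribution is a detail that a condensed article commonly leaves to the full analysis plan, which is not shown and may specify 6-df, cluster-level or permutation inference. The model class itself is sound. A normal-quantile formula with a design effect is a common planning shortcut and does not bind the later test. At the planned ICC the inflation is modest, and by likelihood ratio it is about half a point.

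Most of this stands. A reader might infer from the z-based sample size that uncorrected Wald tests are planned, but the document does not say so; the accurate statement is that no method is named. A reader might also infer that the error rate doubles. That needs an ICC of 0.05, which is five times the planning value and appears nowhere in the document.

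What does not fall away is the sample-size side. The 80% power is stated, and it rests on a large-sample reference for 8 practices. If an unseen plan adopts a 6-df reference, the stated power is wrong for that analysis. The point therefore does not rest on silence alone.

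**Conclusion.** The concern holds in a limited form. The stated power takes no account of there being 8 clusters, and the named model has no stated protection against the same problem. Under default Wald z inference the false-positive rate is about 6–7% at the planned ICC; the higher figures apply only if the ICC is larger than planned. At ICC 0 there is no inflation.

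The error rates rest on simulations without the planned covariate adjustment and without the constrained allocation, both of which would change the exact values. The linear and count models face the same shortage of clusters but were not simulated, so no size can be put on the effect there. The power figures are analytic and apply to the planned 108 Māori infants per arm. The article reports 251 women in the intervention primary cohort but not how many are Māori, so power at the achieved size cannot be computed. Nothing can be concluded against a permutation test over the constrained allocations, because the length of that list is not given.

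This should be clarified before analysis. It is not a reason to reject the design or the model.

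**What to change.** In Analysis, state that inference on the primary outcome uses a few-cluster reference. The preferred form is a two-stage cluster-level analysis: covariate-adjusted practice summaries compared by a t test on 6 df, with fewer df if practice-level covariates are included. Without covariates, this kind of test stayed close to 5% in every setting simulated. The alternative is the mixed model with between-within degrees of freedom, noting that it is conservative (about 2%) at ICC 0.01. Apply the same degrees-of-freedom rule to the secondary outcomes. If the full analysis plan already contains such a rule, say so here.

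In Sample Size, restate the power at 108 per arm with a 6-df reference: about 66% rather than 80% at ICC 0.01, and about 42% if the ICC were 0.05.

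The cost is a change of wording and a simple additional analysis, intervals about 25% wider, and a lower stated power. Recruitment has ended, so the power restatement is for honest reporting and does not change the design. The article schedules outcome data collection from early 2022, after its own publication, so at that point the rule could still be fixed before outcomes were seen.

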## Results

This cluster randomized clinical trial is underway with 8 PCPs. Practices have been randomized to either the intervention arm or control arm. Recruitment of women ended in June 2020, with 293 women enrolled in the intervention arm, of which 251 women (the primary cohort) were seen in a PCP before 20 weeks of pregnancy. Data collection will commence in early 2022 and be complete by mid-2023, and the analysis results are anticipated to be published in late 2023. The explicit and conscious decision to use an indigenous lens when analyzing the data allows outcomes to be viewed with a focus on advantage and privilege rather than one of disparity.

## Discussion

Quality, culturally responsive maternal care is expected and essential to the achievement of Māori pregnancy, birthing, and motherhood aspirations of “hapū ora” [19], that is, the health and well-being of Māori mothers-to-be and their babies. Pregnancy is an important period during which health and support services can provide information, care, and resources to enable the optimal environment for fetal and neonatal stages of life [19]. Quality antenatal care is especially important as part of a continuum of health care for mothers and as the starting point for the child’s developmental trajectory [20]. Māori women have a higher prevalence of maternal risk factors compared to other women and have greater maternity needs [21]; yet, their access to maternal health care and social support does not reflect this. As primary maternity care is considered to be a key enabler of health and well-being, it is pivotal that we find structural solutions that support hapū ora [19].

This augmented pathway enabled through primary care aims to achieve equitable outcomes by meeting the structural determinants and health needs of pregnant Māori women. If successful, the findings of this trial will inform policy makers and service providers to bring about system changes.

### Limitations

The study limitations include whether PCPs find He Korowai Manaaki useful in their practice. Given the heterogeneous make-up of PCPs, the benefits for each practice may vary depending on their population, resources, and needs. The study does not measure which component(s) of the pathway are taken up; however, an intention-to-treat analysis is widely accepted as the gold standard for assessing the superiority of the intervention in randomized trials [18].

Further, this study will be carried out in an urban area with a high Māori population, and the results may not be generalizable to other areas and other communities.

### Conclusions

The results of this study will inform policy and clinical pathways for Māori and be valuable in informing agencies about the potential health and well-being gains from an iwi-initiated augmented national maternity care pathway accessible through primary care.

## Abbreviations

ECE: Early Childhood Education
LMC: lead maternity carer
MOH: Ministry of Health
NHI: National Health Index
PCP: primary care practice
WCTO: Well Child Tamariki Ora
